### Side effects and adverse event reporting

Both types of treatment have been used routinely in our department and specifically by all participating surgeons. The treatments’ risks and disadvantages are therefore not expected to differ from normal patient application outside the trial. All expected and unexpected complications related to the surgical procedure (nerve injuries, deep and superficial infections, malpositioning of the components, and instability) will be recorded systematically by the primary investigator. The patients are routinely asked about complications at each follow-up. Information about hospital contacts related to the surgical procedure is also retrieved from the institutional medical record and from the Danish National Patient Register, which is a nationwide database recording all hospital contacts in Denmark.

Both ORIF and EHA have proven safe in retrospective series from our institution and the study will not be stopped prematurely.

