## Abstract

**Background:**

Intraarticular distal humeral fractures of AO/OTA type 13 C2 and C3 pose a surgical challenge despite the evolution of surgical implants and techniques. Open reduction and internal fixation (ORIF) is often preferred as the first choice of treatment, but the results vary and are sometimes disappointing. Total elbow arthroplasty (TEA) has been widely used for fractures that are not amenable to ORIF in elderly patients, but the mechanical complications remain a challenge, especially in active patients. Elbow hemiarthroplasty (EHA) provides a modern alternative that might avoid the mechanical complications and weight bearing restrictions related to the linked articulation in semi-constrained TEA. No studies have compared the results of EHA to that of ORIF, but case series have reported promising results.

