#### Complications and reoperations

We will record all complications related to the surgical procedure (nerve injuries, deep and superficial infections, malpositioning of the components, and instability) and reoperations (defined as any surgical intervention to the index elbow after the primary procedure).

Length of sick leave will be recorded.

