### Follow-up

All patients will be followed actively for 10 years. To ensure the implant position, all patients will undergo a plain x-ray in two planes before discharge, which will usually be done on the first postoperative day. Then all patients will be followed actively with plain radiographs, clinical outcome, and patient-reported outcome at 3 months postoperatively and at 1, 2, 5, and 10 years.

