#### Data analysis

No interim data analysis will be carried out before the analysis at 2 years. Baseline characteristics and outcome scores will, for each group, be summarized by number and percentage (categorical data) and mean and standard deviation or median and interquartile range, as appropriate (continues data). No statistical tests of differences in baseline characteristics between the two groups will be conducted as any difference must be due to chance and not bias. The differences in outcome scores between the two groups will be analyzed with use of parametric statistics (Students *t*-test) or non-parametric statistics (Mann-Withney U-test) as appropriate. Categorical data will be analyzed with use of chi-square test.

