### Trial status

Protocol version 4.

Issue date: 28/04/2020, author [name].

Inclusion started on February 1, 2020. Finnish date of recruitment of all patients is expected to be at December 31, 2022. In case the target number of 44 patients has not been met, the recruitment period may be extended to reach the number required. The trial processes will be monitored by the primary investigator and the study group to ensure the protocol. If any changes are necessary, the primary investigator is obliged to inform The Scientific Ethical Committee of the Capital Region of Denmark and Data Protection Agency.

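### The plan promises unconditionally not to stop early, on grounds that do not address the comparative safety of EHA and ORIF, and describes no route for accumulating complication data to pause recruitment

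*Protocol article*

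**What the plan says.** All of this is in the protocol article.

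- *Side effects and adverse event reporting* fixes the rule without condition: "Both ORIF and EHA have proven safe in retrospective series from our institution and the study will not be stopped prematurely". Earlier in the section a second ground is given: both operations are routine in the department and for every participating surgeon, so risks should match those outside the trial.
- The same section describes safety data collection. Complications "will be recorded systematically by the primary investigator", and "The patients are routinely asked about complications at each follow-up". The medical record and the national patient register add to this.
- *Complications and reoperations* adds "reoperations (defined as any surgical intervention to the index elbow after the primary procedure").
- *Follow-up* sets visits "at 3 months postoperatively and at 1, 2, 5, and 10 years".
- *Data analysis*: "No interim data analysis will be carried out before the analysis at 2 years".
- *Trial status*: "The trial processes will be monitored by the primary investigator and the study group to ensure the protocol". Any necessary change must be notified to the ethics committee and the data protection authority, and recruitment may be extended until 44 patients are reached.
- *Abstract, Background*: "No studies have compared the results of EHA to that of ORIF, but case series have reported promising results". The abstract's *Discussion* hypothesises fewer complications with EHA than with ORIF.

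**The concern.** This is a rule that the article states, so it cannot be set aside as detail left to a fuller document. It settles in advance that the trial runs to completion, and the reasons offered are about each operation taken alone. Retrospective series and surgeon familiarity can show that each procedure has an acceptable record in ordinary use. They cannot show that the two are similarly safe in the patients randomised here, and the trial's own hypothesis is that complications differ between arms.

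Two things are at stake. First, if nerve injury, deep infection, instability or reoperation accumulated in one arm, the plan gives nobody the task of looking at the counts by arm or the authority to pause. Second, if the investigators did feel obliged to halt, they would be reversing a published commitment while unblinded and without an agreed process. That would be hard to defend as unbiased.

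**Working it through.** There is no figure in the plan to reproduce for this point. What can be checked is whether useful safety data would exist while many patients are still to be randomised, and whether any other section supplies a route to a pause.

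**Inputs.** Total 44, in two equal groups (*Randomization and concealment of allocation*). Recruitment from 1 February 2020 to 31 December 2022, i.e. 35 months, with 15 to 20 such fractures treated per year (*Eligibility*). Visits at 3 months and at 1 and 2 years (*Follow-up*). Assumptions: even accrual and no drop-out.

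**Planned window.** Rate = 44 / 35 = 1.257 patients per month. At month *t*, the number randomised is 1.257 × *t*, and the number past a visit at *m* months is 1.257 × (*t* − *m*).

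| Month 18 | Calculation | Patients |
|---|---|---|
| Randomised | 1.257 × 18 | 22.6 |
| Past 3 months | 1.257 × 15 | 18.9 |
| Past 1 year | 1.257 × 6 | 7.5 |
| Still to be randomised | 44 − 22.6 | 21.4 |

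At the end of recruitment, 1.257 × 23 = 28.9 have passed 1 year.

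**Sensitivity to the rate.**
- At 15 per year (1.25 per month), 44 patients take 35.2 months. Half are in at month 17.6, when 1.25 × 14.6 = 18.3 have passed 3 months.
- At 20 per year (1.667 per month), 44 patients take 26.4 months. Half are in at month 13.2, when 1.667 × 10.2 = 17.0 have passed 3 months.
- Slower accrual gives more follow-up at the halfway point, so an extended recruitment period would strengthen the point.

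**What a review at 11 per arm could show.** With all events in one arm, the two-sided Fisher p-value is 2 × C(11,k) / C(22,k):
- 0 v 4 events: 2 × 330 / 7315 = 0.090
- 0 v 5 events: 2 × 462 / 26334 = 0.035

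A safety judgement need not wait for p < 0.05, but only a gross imbalance would stand out.

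**Is there another route?**
- The monitoring in *Trial status* is directed at trial processes and adherence to the protocol, and does not mention safety by arm.
- *Data analysis* rules out interim analysis before 2 years.
- The allowance to convert ORIF to EHA (*Protocol violations, patient drop-out, and revision*) concerns one patient's operation, not the conduct of the trial.
- The duty to notify changes in *Trial status* leaves a change of plan open, but says nothing about what would prompt it or who would decide.

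**The case against.** The strongest defence has five parts.

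1. **The rule has more behind it than the series.** A reader might infer that retrospective series are its only basis. They are not: the section also relies on routine use, and the operations are done by three experienced surgeons at a large referral unit. That stands, and it justifies light oversight. It still does not speak to EHA against ORIF.
2. **The trial is not locked in.** A reader might infer that recruitment cannot be halted and must run to 44 whatever happens. The documents do not support that, because *Trial status* allows necessary changes with notification. The sentence may also have been meant only to say that no early termination is planned, in line with the absence of an interim analysis. As written, though, it carries no exception.
3. **Individual patients are protected.** They may withdraw at any time, an ORIF can be converted, and reoperation is allowed with the patient kept in the study. This limits the safety concern but does not replace a look at the two arms together.
4. **Detailed safety monitoring belongs in the full protocol.** Agreed: the absence of a monitoring committee, charter or numerical boundary from a condensed article is no finding. The point rests on the stated commitment.
5. **A review has weaknesses of its own.** It would have little power to discriminate, it would be discretionary, and it would not be neutral for the primary analysis: a halt reduces the sample, and complications plausibly correlate with the OES. These are real costs and belong in the fix.

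**Conclusion.** The point holds as a badly fixed rule. The article commits the trial unconditionally not to stop early, for reasons that do not bear on comparative safety, and describes no route by which recorded complications and reoperations could pause recruitment. Under even accrual (an assumption), about 19 patients have passed 3 months at month 18 while about 21 are still to be randomised. At the halfway point the 3-month count is about 17 to 18 across the stated 15 to 20 patients per year.

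It goes no further than that. Nothing in the documents suggests that either operation is unsafe. The lack of an interim efficacy analysis is not a fault: under the planned accrual no patient has reached the 2-year primary endpoint at the halfway point. The patient counts show that data would exist, not that a difference between arms would be detected. This is a worthwhile, inexpensive improvement and does not invalidate the design.

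**What to change.** In *Side effects and adverse event reporting*, replace the clause on premature stopping with a statement to this effect: no early stopping for efficacy or futility is planned; the existing study group will periodically review cumulative complications and reoperations by arm, without looking at the OES; and on a serious safety concern it may pause recruitment and report to the Scientific Ethics Committee. The review interval is for the study group to choose and state.

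The cost is one paragraph and a periodic table of data already being collected, with no new staff. The protocol should acknowledge three downsides:

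- With about 11 per arm, only a gross imbalance would be visible, so the review is a matter of judgement and not a formal test.
- A permanent halt would reduce the sample and the power for the OES. Stopping at 22 patients would leave about 11 per arm against the 18 per group calculated.
- *Blinding* promises a blinded data analysis. The surgeons and primary investigator are already unblinded, but whoever performs that analysis should not see the by-arm tables.

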### Statistics

#### Sample size calculation OES

Oxford elbow score (OES) will be used to measure the primary outcome.

Sample size calculation was performed with a standard deviation (SD) of 16, a MCID of 15, a significance level at 0.005, and power of 0.80, resulting in 18 participants in each group (44 participants in all with allowance for 18% drop-out).

The estimation of SD = 16 is extrapolated from a study on 24 patients with distal humeral fractures treated with EHA [1]. There is no MCID defined for the total score of OES, but Dawson et al. have reported the MCID for each of the three domains—pain, function, and social-psychological—for a group of patients with different pathologies including TEA for osteoarthritis and rheumatoid arthritis. MCID for the three domains is 19, 9, and 18, respectively [5]. Accordingly, we chose the MCID to be 15.

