### Randomization and concealment of allocation

Based on the sample calculation, we intend to include a total number of 44 patients allocated into two groups of equal size:
EHA (elbow hemiarthroplasty)—intervention groupORIF (open reduction and internal fixation)—comparator group

The randomization is done just prior to the operation by the primary investigator, who will inform the operation team about the intended surgery. The randomization sequence will be computer generated using RED-Cap (Research Electronic Data Capture) program. The patients will be randomized using stratified, block randomization with a 1:1 allocation ratio and stratified according to age in years (50–69, 70 and above) and sex. The randomization sequence is generated by a statistician, and the patients will be stratified and then randomized. After randomization, the patient’s allocation will be revealed to the operation team to unpack the necessary operation tools and prosthesis.

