#### Hypotheses

We hypothesize that at 2 years, EHA provides a superior OES compared with ORIF by at least a difference of 15.

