## Discussion

We will attempt to avoid the type-II error (when the hypothesis testing does not reject the null hypothesis, even though the null should have been rejected) by using a proper sample size and by adding 18% to sample size compensating for drop-outs. The drop-out bias will be minimized by obtaining permission to call patients who do not show up for subsequent follow-up and also to visit the patients at home. Selection bias will be avoided through randomization. If ORIF during the surgery is regarded to be technically impossible, the procedure can be converted to EHA. In order to follow the principle of the intention-to-treat, the patient will continue to be in the ORIF group and included in the analysis according to the randomization. A secondary analysis will be conducted on a per protocol basis where only patients who undergo surgery according to the randomization are included.

The consequences of having unblinded patients are unknown. It may introduce bias to the study, which, in most cases, will be in favor of the intervention. In the present study, the intervention and the comparator are surgery and the patients and blinding of the patients may not be as important as in studies where surgery is compared with non-surgery. The primary outcome is a patient-administered questionnaire and does not involve any persons affiliated with the study. It was chosen as the primary outcome to avoid observer bias. The secondary outcomes are not observer blinded and the results will be interpreted carefully due to the risk of bias.

The trial will provide high-quality evidence regarding the short- and long-term clinical and patient-reported outcomes of ORIF and EHA. We use the same outcome scores as in previous randomized trials comparing TEA and ORIF [8, 9, 17]. This makes it possible not only to compare the results but also to include the results in future systematic reviews and meta-analyses. We believe that the results from the present trial, together with results from other randomized trials, can be used to establish a treatment algorithm for distal, intraarticular humerus fractures.

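### The stated significance level of 0.005 does not give 18 per group: at that level power is about 44%, not 80%, and 18 is the answer for 0.05

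*Protocol article*

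**What the plan says.** The section on the sample size calculation for the Oxford Elbow Score (OES) gives every input together. The spread is fixed first: "Sample size calculation was performed with a standard deviation (SD) of 16". The remaining inputs and the result follow: "a MCID of 15, a significance level at 0.005, and power of 0.80, resulting in 18 participants in each group". The total of 44 then allows for 18% drop-out.

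The Data analysis section names a Student t-test or a Mann-Whitney test for outcome scores and gives no significance level. The 0.005 in the sample size section is therefore the only level in the article. Sidedness is not stated anywhere. The Hypotheses section is worded in one direction: "EHA provides a superior OES compared with ORIF by at least a difference of 15".

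The Discussion relies on this calculation. It says that type II error will be countered "by using a proper sample size and by adding 18% to sample size compensating for drop-outs".

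**The concern.** A level of 0.005 is ten times stricter than the usual 0.05, and the article gives no reason for it. With a standardised difference of 15/16 = 0.94, a group size of 18 looks like the answer for 0.05. Either the level or the sample size is therefore wrong.

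The two possibilities have different consequences. If the primary test is run at 0.005 as printed, the trial is far from 80% power, and the Discussion's assurance about type II error is not met. If 0.05 was meant, the only published level is wrong by a factor of ten. A 2-year difference of roughly 11 to 16 points could then be called significant or not depending on which level is applied. A correction made after the results are known would look like relaxing the criterion.

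**Working it through.** **Inputs.** SD 16, difference 15, significance level 0.005, power 0.80 and 18% drop-out come from the sample size section. The 1:1 allocation comes from the randomisation section, and the t-test from Data analysis. Sidedness is not given; two-sided is assumed and one-sided is also tried.

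**Reproducing the plan's figure.** The normal formula per group is n = 2 × [(z₁₋α/₂ + z₀.₈₀) × 16/15]².

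- α = 0.05: 2 × [(1.960 + 0.842) × 1.0667]² = 17.86, rounded up to **18**. This is the stated number. A one-sided 0.025 is the same calculation.
- α = 0.005: 2 × [(2.807 + 0.842) × 1.0667]² = 30.29, rounded up to **31**.

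The drop-out step is correct: 36/(1 − 0.18) = 43.9, so 44. The fault therefore lies in the level or in the 18, not in the inflation.

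**Evaluable patients per group needed for 80% power**

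| Level | Normal formula | t-test (noncentral t) |
|---|---|---|
| 0.005 two-sided | 31 | 33 |
| 0.005 one-sided | 27 | 29 |
| 0.05 two-sided | 18 | 19 |

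No variant at 0.005 comes near 18.

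**Power with the planned numbers.** The noncentrality is (15/16) × √(n/2). For n = 18 this is 0.9375 × 3 = 2.81; for n = 22 it is 0.9375 × 3.317 = 3.11.

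| Level | Method | 18 per group | 22 per group |
|---|---|---|---|
| 0.005 two-sided | t-test | 43.8% | 56.2% |
| 0.005 two-sided | normal | 50.2% | 61.9% |
| 0.005 one-sided | t-test | 54.0% | 65.9% |
| 0.005 one-sided | normal | 59.4% | 70.3% |
| 0.05 two-sided | t-test | 78.0% | 85.9% |
| 0.05 two-sided | normal | 80.3% | 87.5% |

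At 0.05 two-sided, the t-test reaches 80.3% with 19 per group, that is 38 evaluable. This allows 6 of 44 to be lost, or 13.6%.

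**What the observed difference must be.** With SD 16 and 18 per group the standard error is 16 × √(2/18) = 5.33. Significance at a two-sided 0.005 needs an observed difference above about 16.0 points, which is more than the 15-point target. At 0.05 it needs about 10.8.

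**Total if 0.005 is really meant and 80% power is wanted.** Normal formula: 62/0.82 = 75.6, so 76. t-test: 33/0.82 = 40.2, so 41 per group and 82 in all (81 if the total is rounded rather than each arm). The plan has 44.

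**The case against.** The strongest reply is that this is a misprint for 0.05. The stated 18 and 44 both follow at that level, so the sample size would be essentially sound. That is the likeliest explanation, but the article does not say so and no other section gives a different level. A suspected misprint in the only stated level still has to be corrected.

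Four narrower points have merit:

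- **The 44% depends on the variant.** Sidedness is unstated and the hypothesis is directional. With 18 per group the range at 0.005 is 43.8% to 59.4%. A missed true effect is more likely than not only under the two-sided t-test. Every value is still far below 80%.
- **The 78% at 0.05 is secondary.** The article names no formula, and 18 is a legitimate normal-approximation answer, one patient per group short of what the t-test needs. This bears on how power is restated and is not a separate error.
- **The analysed number may exceed 36.** The section on protocol violations and drop-out carries the last observation forward and excludes only those lost before 3 months. If losses stay within 18%, between 36 and 44 patients are analysed, and nominal t-test power at 0.05 lies between 78.0% and 85.9%.
- **The level appears as a sample size input, not in the analysis section.** An analysis plan that is not shown may set the test level. That would not remove the contradiction within the printed calculation, and in this article a reader has only 0.005 to go by.

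**Conclusion.** The point holds. With SD 16, difference 15 and equal groups, the stated level, power and group size are incompatible under every standard variant: 0.005 needs 27 to 33 evaluable patients per group, against 18 planned. For a two-sided t-test at 0.005, power is 43.8% with 18 per group and 56.2% with 22.

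If the level was meant to be 0.05 two-sided, 44 patients are adequate, and the stated 80% is about 2 points high for a t-test with 36 evaluable. The figures take the plan's SD and target difference as given. Those for the t-test assume that it, rather than the Mann-Whitney test, is used.

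**What to change.** Confirm which level and sidedness the calculation used, and record the correction before the 2-year data are analysed.

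- **If 0.05 two-sided:** replace 0.005 in the sample size section and state 0.05 two-sided as the threshold for the primary test in Data analysis. Keep 44 patients. Restate t-test power as 78% with 36 evaluable (18% drop-out), 80% with 38 (at most 13.6% drop-out) and 86% if all 44 are analysed.
- **If 0.005 is intended:** state it as the primary-test threshold with its sidedness, and report two-sided t-test power of about 44% with 36 evaluable. Withdraw the Discussion's claim about type II error, or reconsider the sample size, which would be about 76 to 82 in all for 80% power.

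The likely correction is one figure and a restated power. It needs no extra patients; the only cost is a slightly less favourable power statement.
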